### **Allocation**

Participating LTC homes will be allocated to one of the two arms of the study (active/full intervention versus standard education) using a 2:1 allocation ratio, after stratifying on hub, baseline antipsychotic prescription rates (using published CIHI reports), and size (number of eligible patients). A 2:1 allocation ratio will be used to satisfy the requirements of the sponsor and to improve feasibility of recruitment of homes. LTC homes that share prescribers will be allocated as a unit to avoid contamination. Due to funding restrictions, no more than 38 homes will be allocated to the intensive intervention; if more than 60 homes are recruited, the allocation ratio will be less than 2:1, but the odds of allocation to the full intervention will remain greater than 1:1. Allocation will be conducted by an independent statistician using computer-generated random numbers.

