### **Analysis**

Descriptive statistics will be calculated for all variables of interest: continuous variables with a normal distribution will be described using means and standard deviations (medians and inter-quartile ranges in the case of skewed distributions), whereas categorical variables will be summarized using frequencies and proportions. All analyses will be by Intention To Treat. Analyses will be conducted using SAS v.9.3 and statistical significance will be assessed at the 5% level.

The **primary outcome** describing **dispensing of medication** (number of days with antipsychotic/benzodiazepine/antihypertensive/anticholinergic prescriptions in the last week) will be analyzed using generalized linear mixed effects regression with multinomial distribution and cumulative logit link. To account for the staggered implementation of the intervention, phase (phase1/phase2) will be included as a fixed effect. Random intercepts and slopes will be specified to account for intracluster

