**Secondary clinical outcomes** measured as continuous variables (e.g., ADL, depression score) will be analyzed using linear mixed effects regression with normal distribution and identity link. Fixed and random effects will be specified as described for the prescribing outcomes. The effect of the intervention will be expressed as adjusted least square mean differences with 95% CI. Secondary clinical outcomes measured on an ordinal scale (e.g., pain scale) at baseline, 3 months and 6 months will be analyzed using generalized mixed effects regression as described for the primary outcome but using multinomial distribution and cumulative logit link. Presence of any falls in the past 30 days will be analyzed at baseline, 3 months, and 6 months using generalized linear mixed effects regression with binomial distribution and logit link, as described for the primary outcome. In the Intent-To-Treat analyses for the secondary clinical outcomes (e.g., ADL, falls, pain), the potential effect on inferences of patients who died will be examined using sensitivity analyses under conservative assumptions: for example, patients who died during the interval will be assigned the worst possible score. Depending on the extent of patient turnover within homes, additional analyses for primary and secondary outcomes will explore inclusion of subject-specific random effects to account for repeated measures on the same patient over time (i.e., a cohort rather than cross-sectional design).

**Health care utilization outcomes** (number of ER visits and hospital visits) will be analyzed at 6 months using generalized linear mixed-effects regression with Poisson or negative binomial distribution and log-link, with log person-time of follow-up as an offset term. The following fixed effects will be included: intervention, phase, and stratification variables, as well as the rate of health care utilization at the home 6 months prior to the intervention. Patient covariates will be adjusted for as specified for the primary outcome. Home will be included as a random effect. The effect of the intervention will be expressed as adjusted Rate Ratio (RR) with 95% CI.

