### ***Power***

Our sample size is determined primarily by pragmatic considerations and logistical constraints. A total of **58 LTC homes** will be included in the trial: a maximum of 38 homes allocated to receiving the full intervention and 20 homes to receiving usual care. After grouping homes sharing providers together, we anticipate a total of 45 independent clusters (30 intervention, 15 control). For our primary outcome measured as an **ordinal** variable (number of days with antipsychotic prescription in the past 7 days), 45

homes with 2:1 allocation will yield 80% power to detect a cumulative Odds Ratio (i.e., odds of being in a higher category) of 0.6, assuming an intracluster correlation coefficient (ICC) of 0.01 and an average of 120 residents per home. Assuming that 30% of control arm patients will have 7 days of antipsychotic prescriptions, an OR of 0.6 implies a reduction in this proportion in the intervention arm to 20%.

To ensure we will be able to detect clinically important differences with adequate power for our secondary prescribing outcome (measured as a **dichotomous** variable), we used a simulation study with 1000 simulation runs to determine the required effect size (difference in change from baseline to 6 months in antipsychotic prescribing between the arms) that can be detected with at least 80% power. For this simulation, we assumed a conservative ICC of 0.1, an average of 120 residents per home, and a control arm proportion of 30%. With 45 homes (30 intervention, 15 control), we will have **83.4%** power to detect an OR of approximately 0.75 at 6 months. Assuming a control arm proportion of 30%, this OR corresponds to a reduction in the intervention arm to approximately 25%.

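### The model for ER visits and hospitalisations takes the home as its only random effect, although homes sharing prescribers are randomised together: about 58 homes form about 45 independent units.

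*Protocol*

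**What the plan says.** Three places in the protocol bear on this.

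- **Allocation.** "LTC homes that share prescribers will be allocated as a unit to avoid contamination". The randomised unit is therefore a group of one or more homes.
- **Power.** The trial plans "a maximum of 38 homes allocated to receiving the full intervention and 20 homes to receiving usual care", which makes 58 homes. It then says: "After grouping homes sharing providers together, we anticipate a total of 45 independent clusters (30 intervention, 15 control"). By the protocol's own account, homes and independent clusters are different things and differ in number.
- **Analysis, health care utilization outcomes.** For counts of ER visits and hospitalisations: "Home will be included as a random effect". The fixed part is given as follows, where the closing figure counts months before the intervention: "The following fixed effects will be included: intervention, phase, and stratification variables, as well as the rate of health care utilization at the home 6". In addition, the model adjusts for patient covariates. No term, nesting level or robust variance is given for the prescriber-sharing group.

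For the primary outcome, the same section says "Random intercepts and slopes will be specified to account for intracluster" and inter-period correlations, without naming the level. The prescribing and clinical models refer back to that specification. The general rule is that "statistical significance will be assessed at the 5% level".

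**The concern.** In a cluster trial the treatment contrast varies only between randomised units. If the highest random effect sits below that unit, homes allocated together count as separate pieces of evidence. Any outcome variation they share is left out of the standard error of the treatment effect. Here the protocol's own reason for joint allocation, common prescribers, is also a reason to expect some shared variation.

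At stake are confidence intervals that are too narrow, and a false-positive rate above the nominal 5%, for the adjusted rate ratios for ER visits and hospitalisations. The protocol also lists health care utilisation among the inputs to its cost-effectiveness analysis.

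This is not a complaint that detail is missing. The protocol fixes the random effect explicitly, and fixes it at a level other than the randomised one.

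**Working it through.** **Counts (Power section).** Homes: 38 + 20 = 58. Independent clusters: 30 + 15 = 45. Both totals reproduce. The grouping itself cannot be checked, because the protocol does not say which homes share prescribers. A two-group comparison has 58 − 2 = 56 degrees of freedom at home level and 45 − 2 = 43 at unit level, before covariates. The two-sided 5% critical values are 2.003 and 2.017, so the degrees of freedom matter little. The effect comes through the standard error.

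**Assumptions, none given by the protocol.**
- Sharing is in pairs only. To fit 20 homes into 15 units, the control arm needs 10 single homes and 5 pairs. To fit 38 homes into 30 units, the intervention arm needs 22 single homes and 8 pairs.
- Home means have equal variance (set to 1) and correlation κ between two homes in the same unit, zero otherwise.
- The test is an unadjusted two-sided t test on home means. It stands in for the planned Poisson or negative binomial mixed model.

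**Formula.** With n homes in an arm and p pairs, the true variance of the arm mean is (n + 2pκ)/n². A home-level analysis uses 1/n.

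- Home-level variance of the difference: 1/20 + 1/38 = 0.0500 + 0.0263 = 0.0763.
- True variance at κ: (20 + 10κ)/400 + (38 + 16κ)/1444.

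| κ | True variance | Ratio to 0.0763 | True SE / home-level SE | 2.003 ÷ SE ratio | Two-sided tail, t on 56 df |
|---|---|---|---|---|---|
| 0 | 0.0500 + 0.0263 = 0.0763 | 1.000 | 1.00 | 2.003 | 5.0% |
| 0.3 | 0.0575 + 0.0296 = 0.0871 | 1.142 | 1.07 | 1.875 | 6.6% |
| 0.5 | 0.0625 + 0.0319 = 0.0944 | 1.236 | 1.11 | 1.802 | 7.7% |

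**Check by simulation.** Simulated null trials with the same layout give 6.6% at κ = 0.3 and 7.7% to 7.8% at κ = 0.5 for the home-level test. A test on the 45 unit means stays at about 5% throughout. At κ = 0 the home-level test is also at about 5%, so there is no inflation without residual correlation.

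**The case against.** **Home may be loose wording for the cluster.** The Power section groups homes into 45 clusters and then, in its power statements, calls those 45 units homes. The authors knew of the grouping and powered on it, so the utilisation model might mean the grouped unit too. This is the best point on the other side, but it does not settle the matter. The same Power section separates 58 homes from 45 clusters, and the same model takes the prior utilisation rate at the home as a covariate, which reads as the individual facility. On the kinder reading the sentence still needs correcting, because an analyst following it literally would fit the wrong level.

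**Adjustment may remove the problem.** The model includes the home's own prior rate, the stratification variables (hub among them), phase and patient covariates. These should absorb part of what homes in a unit share. Shared prescribers also bear more directly on prescribing than on ER visits or admissions. This stands: the inflation is conditional on what correlation remains, and could be small.

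**Stronger readings that the documents do not support.**
- A reader might infer that the primary analysis has the same fault. The protocol does not say so. The primary, prescribing and clinical models refer to intracluster correlation without naming a level, and the Power section uses cluster for the grouped unit.
- A reader might infer that home is the only random effect named anywhere. It is the only cluster-level unit named, but the Analysis section also mentions subject-specific random effects for additional analyses.
- A reader might assume large sharing groups, or homes in a unit that are perfectly correlated, and arrive at much higher error rates. The protocol describes no such groups, and its Recruitment section favours low prescriber overlap when further homes are sought. A correlation of 1 between home means would also require no sampling error within homes. With the protocol's 120 residents per home and its prescribing ICCs, borrowed here only as an illustration, the ceiling is 0.01/(0.01 + 0.99/120) = 0.55 at ICC 0.01 and 0.1/(0.1 + 0.9/120) = 0.93 at ICC 0.1, even if all between-home variance were shared.

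**Conclusion.** Wrong as written, for two secondary outcomes: ER visits and hospitalisations. The model's only stated random effect is below the unit of randomisation, by the protocol's own distinction between 58 homes and about 45 clusters.

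The direction is clear if homes in a unit remain positively correlated after adjustment: standard errors too small and type I error above 5%. The size is not known. The pairs calculation gives about 5% to 7.7% for correlations from 0 to 0.5. It rests on an assumed grouping, an assumed correlation and an unadjusted test on home means, so it is an illustrative range and not an estimate for the planned model. The figure of 45 is itself an anticipated count.

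**What to change.** - **Analysis, health care utilization outcomes:** name the allocated unit (the prescriber-sharing group, or the single home where nothing is shared) as the random effect, with home nested within it where estimable. If sharing is in pairs, 10 + 22 = 32 of the 45 units hold one home, so the two variance components may be hard to separate. In that case keep the allocated unit alone. Base denominator degrees of freedom on the number of allocated units.
- **Analysis, primary, prescribing and clinical models:** state that intracluster correlation refers to the same allocated unit.
- **Power:** where the 45 units are called homes, call them clusters.

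No new data are needed, because allocating homes as units already requires the grouping. The cost is one line per model and somewhat wider confidence intervals. In the pairs illustration the standard error rises by about 7% at correlation 0.3 and 11% at 0.5.

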### ***Antipsychotics: evidence for interventions to reduce prescribing in LTC***

In a systematic review conducted by Thompson Coon and colleagues (2014) on interventions to reduce inappropriate prescribing of antipsychotics among people with dementia in LTC homes, a 12-20% reduction in antipsychotic prescribing levels was found. The type of intervention implemented has an effect on the size of improvements in initiatives targeting antipsychotic improvement in LTC homes. In a systematic review of interventions to optimize prescribing in LTC homes, academic detailing was found as having the strongest evidence for improvements in prescribing, whereas audit and feedback interventions provided small to moderate impact on physician practices (Loganathan et al., 2011). Furthermore, according to Milta and colleagues (2013), educational outreach interventions demonstrate improvements ranging from 18 to 19 percent reductions in antipsychotic use compared to geriatric assessment alone. It has been recommended that in order for educational interventions to be effective at improving inappropriate prescribing, they must be implemented alongside complementary techniques such as academic detailing (Loganathan et al., 2011; Milta et al., 2013). The development of a tracking mechanism that includes specific outcome measures is also recommended (Milta et al., 2013). A randomized control trial in which staff was randomly assigned to receive quarterly audit and feedback plus education about quality improvement demonstrated a decrease in resident falls, behavioural symptoms and pressure ulcers (Rantz et al., 2001).

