### **Objectives**

This pragmatic, cluster randomized controlled trial seeks to assess the impact of an intervention that could be readily implemented at scale to improve appropriateness of prescribing. The policy-makers previously determined that all LTC prescribers in the province would be provided with the opportunity to access online practice reports (audit and feedback) that would confidentially describe their prescribing practices for antipsychotic medications, compared to (de-identified) peers. In addition, based on evidence suggesting the potential synergistic effects of audit and feedback with educational outreach (Ivers et al., 2012; Avery et al., 2012), policy makers decided that an educational outreach should be included as part of an ‘Appropriate Prescribing Demonstration Project’.

This proposal forms one part of a program evaluation for the Demonstration Project; given the costs inherent in delivering educational outreach, a rigorous design to assess the added impact of this intervention is desirable. A mixed methods formative evaluation and process evaluation are planned to understand how and why program effects were observed and provide insights regarding scale-up of the interventions.

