**Design**

Two arm, pragmatic, cluster-randomized trial, with LTC homes allocated to the full, active intervention (featuring educational outreach offered to each prescriber and team members in the home) or standard quality improvement supports (including online audit and feedback reports for each prescriber in the home). The ‘standard’ quality improvement supports represent ‘usual care’ as these are to be launched province-wide; a concurrent control arm with no exposure to a quality improvement intervention is not feasible.

[ClinicalTrials.gov NLM Identifier: NCT02604056]

[figure not shown]

To evaluate the secondary aim of how and why the interventions work as observed, we will employ an embedded single case design with cross case synthesis to gain an in-depth understanding of the conditions and factors associated with implementation of the intervention. The embedded design enables the examination of interactive processes and contextual features through various units of analysis derived from a structured approach to develop programme theory (Davidoff et al., 2015; Portela et al., 2015; Reed et al., 2014). Normalization Process Theory (NPT) and the Consolidated Framework for Implementation Research (CFIR) will be used to guide and structure data collection methods and data analysis. NPT is an established framework for understanding how and whether complex interventions become embedded in health care practice—that is, normalized (Macfarlane et al., 2012). This approach is ideally suited to this study as it entails numerous individuals, professionals, unit, organizational and health systems features that may impact the effectiveness of the audit and feedback intervention in selected LTCs. The CFIR provides a comprehensive taxonomy of defined constructs that are likely to influence implementation (Damschroder et al., 2009). Its application facilitates the identification of active components and further explores the setting in which the intervention is delivered.

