### **Interventions**

### ***Standard quality improvement supports / Usual care:***

Numerous quality improvement initiatives are simultaneously occurring in the LTC sector related to appropriate prescribing, making a randomized comparator all the more important. For instance, CIHI is reporting on antipsychotic use and antipsychotic prescribing has been named a 'priority indicator' for mandatory annual quality improvement plans to be completed by each LTC.

Starting in autumn 2015, in concert with the initiative outlined in this proposal, HQO will be producing confidential **practice reports** using data from ICES to describe selected quality indicators for LTC physicians. This will initially focus on appropriate prescribing of antipsychotics for older men and women with dementia, with an initial focus on how their antipsychotic medication use compares to others in the province plus additional information regarding the clinical and demographic features of their LTC patient roster. Receipt of the reports is voluntary. To receive the reports, physicians must sign up and confirm their identity. They will then receive updated reports quarterly, which they can download from HQO's secure website. In addition, HQO will be launching voluntary, virtual 'communities of practice' to enable sharing of best practices across homes and providers. Starting in autumn 2016, HQO will introduce additional indicators to the practice reports, including benzodiazepines, antihypertensives, and anticholinergic medications.

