Potential effect modification by ownership status of LTC home and staffing ratios, size of the home (<65 beds, 65-129 beds, or >129 beds), location (urban/rural), specialist utilization (proportion of patients with geriatrician or psychiatrist consultation within 6 months), plus primary physician characteristics (sex, years' experience), as well as patient characteristics (age, sex, time at facility, levels of function and aggressive behaviour plus whether a geriatrician or psychiatrist provided a consult) will be explored by including interactions between these variables and: time, treatment, and treatment by time.

Although primary analyses will examine outcomes for all patients excluding those with known to be palliative or with a history of bipolar disorder, schizophrenia or Huntington's disease, planned sub-group analyses will focus on those with dementia. A planned sensitivity analysis will restrict the educational

outreach cohort to physicians who also accessed the audit and feedback to examine for synergy in the full intervention group. We do not anticipate substantial missingness on prescribing or health care utilization outcome; however, exploratory analyses will be carried out to identify the extent of missing data on resident clinical and demographic variables (e.g., levels of function, aggressive behaviour, depression). If more than 5% of residents have missing data at any time, we will create a complete data set for analysis using multiple imputation, where the imputation model will include all covariates of interest in subsequent primary and secondary outcome analyses, as well as those variables identified as associated with missingness.

Since the CCRS data is only released for linkage at ICES annually, a planned interim analysis will compare the primary and secondary prescribing outcomes (which use ODB data). No stopping rules are planned based on this interim analysis; the results will be considered tentative and used only for confidential reporting to the funders.

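### The synergy sensitivity analysis restricts only the outreach arm to report users, so it is biased towards apparent synergy if report users improve more than non-users

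*Protocol*

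**What the plan says.** The rule is one sentence in the protocol's Analysis section. It begins "A planned sensitivity analysis will restrict the educational" and continues "outreach cohort to physicians who also accessed the audit and feedback to examine for synergy in the full intervention group". Nothing is said about how control physicians are handled in this analysis.

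Three other places bear on it:

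- The Design section describes the control condition as "standard quality improvement supports (including online audit and feedback reports for each prescriber in the home". Control physicians therefore also divide into those who use the reports and those who do not.
- The usual-care part of the Interventions section makes use a matter of choice: "Receipt of the reports is voluntary. To receive the reports, physicians must sign up and confirm their identity".
- The Objectives section gives "potential synergistic effects of audit and feedback with educational outreach" as a reason for including outreach, so synergy is a question the project cares about.

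The Analysis section also states "All analyses will be by Intention To Treat", from which this restricted analysis departs.

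**The concern.** Synergy is an interaction: it asks whether outreach does more where the reports are used than where they are not. Answering it needs users and non-users in both arms. The stated rule removes non-users from one arm only. The resulting contrast can contain three things that it cannot separate: any genuine synergy, the effect of the reports on those who read them, and the kind of physician who signs up.

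The likely direction of the bias can be read from the protocol itself. Its background section says that "audit and feedback interventions provided small to moderate impact on physician practices". On that view report users should improve more than non-users even without outreach, and the one-arm restriction would credit that improvement to the combined intervention.

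Timing adds to the problem. In the Implementation section the reports open in September 2015, in the same two-month period as the Phase 1 allocation. For those homes access is largely a post-allocation behaviour, and outreach may itself prompt it.

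At stake is a misleading statement about synergy. The main treatment comparison is not at stake.

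**Working it through.** The protocol gives no figure for this analysis, so there is none to reproduce. The check asks what the restricted comparison would show if outreach had no effect on anyone.

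**Inputs from the protocol (Power section).** Control proportion 30%. For the simulation below: 30 outreach and 15 control clusters, 120 residents per home, ICC 0.1.

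**Assumptions, none given in the protocol.** A share *a* of physicians uses the reports in each arm. The OR *g* is the change from baseline to 6 months in users' residents relative to non-users' residents. Users and non-users start at the same 30%. The outcome is dichotomous antipsychotic prescribing.

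**Formula.** Apparent OR = odds(users at 6 months) / odds(*a* × users + (1 − *a*) × non-users at 6 months).

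**Worked case, *a* = 0.4, *g* = 0.75.**

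1. Baseline odds: 0.30/0.70 = 0.4286.
2. Users at 6 months: odds 0.4286 × 0.75 = 0.3214, a proportion of 24.3%. Non-users stay at 30%.
3. Control mix: 0.4 × 24.3% + 0.6 × 30% = 27.7%, odds 0.3837.
4. Apparent OR: 0.3214/0.3837 = 0.84.

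**Apparent OR when the true outreach OR is 1:**

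| Access share | *g* = 1.1 | *g* = 1 | *g* = 0.9 | *g* = 0.75 | *g* = 0.6 |
|---|---|---|---|---|---|
| 20% | 1.08 | 1.00 | 0.92 | 0.79 | 0.66 |
| 40% | 1.06 | 1.00 | 0.94 | 0.84 | 0.73 |
| 60% | 1.04 | 1.00 | 0.96 | 0.89 | 0.80 |
| 80% | 1.02 | 1.00 | 0.98 | 0.94 | 0.89 |

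If both arms are restricted to users, the numerator and denominator are the same and the OR is 1.00 for every *a* and *g*, provided access selects the same kind of physician in each arm.

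**How often would this look significant?** A simulation used the protocol's cluster numbers, home size and ICC. It further assumed three physicians of 40 residents per home, a cluster autocorrelation of 0.8 and a cluster-level t test on change in log odds, with 1,500 runs per setting. The nominal rate of a significant result in favour of outreach is 2.5%.

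| Access share | *g* = 1 | *g* = 0.9 | *g* = 0.75 | *g* = 0.6 |
|---|---|---|---|---|
| 30% | 3.3% | 6.3% | 17.6% | 46.0% |
| 50% | 2.4% | 4.7% | 13.4% | 30.1% |

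With both arms restricted, the simulated OR was 0.99 to 1.01 and the rate 2.1% to 2.9%.

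**Stable differences between physicians.** With users lower by 0.4 log odds at both times, no difference in change and 40% access, the one-arm restriction gave an OR of 1.01 and a rate of 1.7%. A level difference alone therefore produces no false signal in a model of change from baseline.

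**The case against.** The strongest reply is that the prescribing models target change over time: the Analysis section names time, intervention and their interaction as the terms of main interest. A stable difference between physicians who open reports and those who do not therefore cancels. This stands. A reader might infer that the analysis would show synergy even if outreach did nothing, but the documents do not support that without a condition. Users must also improve more than non-users. If they change equally there is no false signal, and if they change less favourably the bias runs against outreach. With a mild difference (*g* = 0.9), one reading of the small-to-moderate effect the protocol cites, the bias is an OR of 0.92 to 0.98 and would seldom reach significance.

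Second, the comparator is not spelled out, and a statistical analysis plan that is not shown might restrict the controls as well. That is fair as far as it goes. The accurate charge is that the protocol states a restriction of one arm and no matching one. An unrestricted control arm is the natural reading, and the sentence is a stated rule rather than a detail left open.

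Third, this is one labelled sensitivity analysis. That also stands: the primary estimate, the power and the conduct of the trial are untouched. A reader might further infer that the result feeds the scale-up decision. The Implementation table mentions a possible later launch of outreach if scale-up is approved, but no section ties that decision to this analysis.

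**Conclusion.** The point holds in a conditional form. As written, the analysis cannot isolate synergy, because it selects on a voluntary behaviour in one arm when that behaviour exists in both. It is biased towards apparent synergy if report users improve more than non-users, which is the direction the protocol's own view of audit and feedback leads one to expect. With outreach having no effect and 40% access, the false OR is 0.94, 0.84 or 0.73 for a user OR of 0.9, 0.75 or 0.6. These figures depend on assumed access shares and on reading the user OR as a difference in change from baseline; the protocol gives neither quantity. The primary intention-to-treat result is unaffected. The change is still worth making, since synergy is part of the stated rationale for outreach and the remedy is cheap.

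**What to change.** Replace the one-arm restriction in the Analysis section with one of the following:

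1. **Preferred:** an arm-by-report-access-by-time interaction using all homes. The section already plans interactions of physician characteristics with time, treatment and treatment by time, so report access can be added to that list. This addresses synergy directly because it compares the outreach effect in users with that in non-users.
2. **Alternatively:** the same access restriction in both arms. This estimates the outreach effect among report users; by itself it does not show that the effect differs from that in non-users.

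Define access as sign-up before the home's start date where numbers allow. For control homes, the measurement times that the Outcomes section assigns from intervention homes in the same stratum can supply that date. Where access can only be measured after the start, label the analysis exploratory and non-randomised, because outreach may prompt access. Even with sign-up before the start, access is chosen rather than randomised, so an interaction shows that the outreach effect differs between types of physician and does not prove that the reports cause the difference.

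Using allocation as an instrument for report access would not be a valid way round this. Allocation delivers outreach, which is meant to change prescribing directly, so outreach's own effect would be credited to the reports.

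**Cost:** revised wording and access dates for both arms rather than only the outreach arm. Precision is lower than in the main analysis. Few Phase 1 physicians may have signed up before the start, because the reports open at about the time of allocation. The only audit-and-feedback-only row in the Implementation table is labelled Phase 1, so early sign-ups may be especially few among controls.
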